## Abstract

**Background:** Transient ischemic attack (TIA) has a high incidence of recurrent vascular events. Hypoperfusion is one of the factors that are closely correlated with 7-day recurrence of TIA. This study aimed to evaluate the power of hypoperfusion shown on magnetic resonance (MR) perfusion imaging in predicting the incidence of 7-day recurrence of ischemic events after TIA.

**Methods/Design:** REATTACK is a prospective multi-centered cohort study on the correlation between MR perfusion and TIA recurrence. Ninety patients aged ≥18 years with recent (<7 days after onset) clinical TIA will be continuously included. All the patients will undergo diffusion-weighted imaging (DWI) and perfusion-weighted imaging (PWI) assessments within 24 h after the onset of TIA. The subjects will then be divided into a PWI positive group and a PWI negative group according to the time-to-maximum of the residue function (*T*_*max*_). PWI will be repeated after 7 days and in 3 months. The primary clinical outcome will be the recurrence of TIA within 7 days after the onset of TIA. Secondary outcomes will be the recurrence of TIA in 3 months and modified Rankin scale (mRS) score. A chi-square test will be performed to compare the difference in the incidence of recurrent TIA between the two groups, and rank sum test in the mRS score. Multivariate logistic regression will be simultaneously performed to analyze the risk factors for the recurrence of TIA.

**Discussion:** The results of this study will confirm whether abnormal *T*_*max*_ helps to identify the patients with TIA who have high risks of recurrent ischemic events. This would largely improve the prognosis of patients with TIA.

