## Methods

### Study Design

REATTACK is a prospective cohort study with a 3-month follow-up period. The participants are patients who had TIA within 7 days of onset diagnosed by two neurologists. Brain DWI and PWI assessments will be completed within 24 h of admission, and *T*_*max*_ > 4 s > 10 ml is used to determine the presence of hypoperfusion. According to baseline MRI-PWI examination, the patients are divided into the PWI positive and PWI negative groups. DWI, PWI, fluid-attenuated inversion recovery (FLAIR), and magnetic resonance angiography (MRA) examinations will be repeated 7 days later. The main outcomes are the incidence of recurrent TIA within 7 days and in 3 months, and the mRS score in 3 months.

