### Objectives

#### Primary Objective

▪   To assess the added diagnostic value of hypoperfusion demonstrated on PWI in predicting recurrent vascular events of patients with TIA within 7 days.

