### Sample Size and Power Calculation

Two-sided chi-square test is performed at *P* = 0.05 (alpha) to compare the incidence of recurrent vascular events between patients with TIA with PWI-positive and PWI-negative findings. Previous studies have shown that 10% of patients with TIA will relapse; however, the pilot study showed that 34.8% of PWI-positive patients with TIA had recurrent TIA. With the testing power of 80%, the significance level of 0.05 (two-sided), and a 1:1 ratio, with a dropout rate of 5%, a total of 90 patients are needed to detect the difference in relative risks between patients with TIA with PWI negative and PWI positive findings.

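### The only named primary outcome is recurrent TIA within 7 days, but the primary objective and powered comparison concern recurrent vascular events; read literally, the outcome omits a stroke-only patient

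*Protocol article*

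**What the plan says.** Three descriptions of the event serve one primary question in the protocol article.

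- **Recurrent TIA.** The Abstract states: "The primary clinical outcome will be the recurrence of TIA within 7 days after the onset of TIA". Its analysis sentence follows suit: "A chi-square test will be performed to compare the difference in the incidence of recurrent TIA between the two groups". Study Design uses the same event: "The main outcomes are the incidence of recurrent TIA within 7 days and in 3 months, and the mRS score in 3 months".
- **Ischemic events.** The Abstract gives the aim as "predicting the incidence of 7-day recurrence of ischemic events after TIA".
- **Recurrent vascular events.** The Primary Objective reads: "To assess the added diagnostic value of hypoperfusion demonstrated on PWI in predicting recurrent vascular events of patients with TIA within 7 days". Procedures collects vascular events at the second and third visits. Sample Size and Power Calculation sets up a chi-square test "to compare the incidence of recurrent vascular events between patients with TIA with PWI-positive and PWI-negative findings". Statistical Analysis summarises vascular events at days 7 and 90, and its logistic regression sentence says only recurrence, without naming the event.

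The article does not define a recurrent vascular event, and it does not say that recurrence of TIA includes stroke. The Background defines TIA as an episode without evidence of acute infarction, and it speaks of stroke as one kind of vascular event.

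**The concern.** These terms are not interchangeable under the document's own definitions. A stroke with infarction is a vascular event and an ischemic event, but it is not a TIA. An analyst who follows the sentence naming the primary outcome would not count a patient whose only event within 7 days is a stroke. An analyst who follows the primary objective would count that patient. The two analyses can give different answers, and only the second answers the objective.

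The Background treats stroke as a central early risk after TIA, and it says that hypoperfusion may be associated with stroke as well as with recurrent TIA. The patients in dispute could therefore bear directly on the study question.

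The sample-size section carries the same ambiguity. It compares vascular events, takes its PWI-positive rate from recurrent TIA, and takes its reference rate from an unspecified relapse.

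**Working it through.** **1. Who counts under each wording**

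| Event within 7 days | Recurrent TIA (Abstract outcome, Study Design) | Ischemic events (Abstract aim) | Vascular events (objective, powered comparison) |
|---|---|---|---|
| TIA only | yes | yes | yes |
| TIA and ischemic stroke | yes | yes | yes |
| Ischemic stroke only | no | yes | yes |

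Among these patterns, the wordings part company only on the stroke-only patient.

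**2. The plan's own sample size**

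Inputs from Sample Size and Power Calculation: 10% versus 34.8%, two-sided alpha 0.05, power 80%, 1:1 allocation, 5% dropout, total 90. The difference is 0.248.

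- Arcsine formula: n = 2(1.96 + 0.842)² / h², with h = 2·asin√0.348 − 2·asin√0.10. This gives 41.05, so 42 per group; 42/0.95 = 44.2, so 45 per group and 90 in total. This matches the plan.
- Unpooled variance: n = (1.96 + 0.842)² × (0.10×0.90 + 0.348×0.652) / 0.248² = 40.4, so 41 per group. After dropout this is 44 per group, 88 in total.
- Pooled variance: 44 per group, 88 in total; 88/0.95 = 92.6, so 93.
- Evaluable patients: 90 × 0.95 = 85.5, taken as 86, or 43 per group. Power at 43 per group (pooled) is 79.8%.

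The total of 90 reproduces. The arithmetic is sound; what is unclear is the endpoint to which it applies.

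**3. Events expected at the planning rates**

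43 × 0.348 + 43 × 0.10 = 15.0 + 4.3 = 19.3, about 19.

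**4. Patients whose classification is in question**

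The Background quotes a 4–10% stroke risk within 7 days of TIA.

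- 86 × 0.04 = 3.4 and 86 × 0.10 = 8.6, so about 3 to 9 patients.
- Relative to the planned events: 3.4/19.3 = 18% and 8.6/19.3 = 45%.
- These are upper bounds at each rate, because a patient with both a stroke and a TIA counts either way.
- The Background also quotes 2.1% for recurrent ischemic events under optimal secondary prevention, without a time window: 86 × 0.021 = 1.8, about 2 patients.

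**5. Effect on power if strokes are added to the outcome (illustration)**

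Assumptions: the planning rates describe TIA only, strokes add to them, 43 evaluable per group, pooled formula. The split of strokes between groups is assumed, since the documents give none.

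| Added by strokes (PWI+ / PWI−) | Rates compared | Power | Total N with 5% dropout |
|---|---|---|---|
| none | 34.8% v 10% | 79.8% | 93 |
| +4 / +4 points | 38.8% v 14% | 75.1% | 104 |
| +10 / +10 points | 44.8% v 20% | 69.7% | 116 |
| +6 / +2 points | 40.8% v 12% | 87.1% | 76 |

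Power moves either way, according to how strokes divide between the groups.

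**The case against.** The strongest reply is that this is loose labelling. The objective, data collection and powered comparison all use vascular events, and Procedures asks for etiological subtypes to be considered as reasons for early recurrent stroke, so stroke is plainly foreseen. The article is also condensed, and a full protocol may define the event. Part of this stands. A reader might infer that the study has adopted a rule scoring strokes as non-events; the documents do not say so. The defect is that the stated primary outcome, taken at its word, leaves them out. A possible definition elsewhere does not remove a contradiction in the printed text.

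Other stronger readings also fail:

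- **A stroke hides a later TIA.** Nothing says that follow-up stops at stroke; visits run to day 90 for all patients.
- **The comparison is biased toward the null.** That requires strokes to concentrate in PWI-positive patients. The Background makes this plausible but gives no split.
- **Three to nine patients will be misclassified.** The documents also support lower counts. Besides the 2.1% figure, the Discussion quotes 7.4% stroke at 90 days; 86 × 0.074 = 6.4, which would limit the 7-day count to about 6.
- **The outcome will be chosen after the data are seen.** The study is registered and the record is not shown, so this is speculation.
- **Study Design has three primary outcomes.** It calls them main outcomes, and they are broadly those the Abstract ranks as primary and secondary. This is a minor clarity point.

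It is also fair to say that the documents do not dictate one particular composite. They call for a single defined outcome that answers the stated objective.

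**Conclusion.** The concern holds as a contradiction about the primary outcome. The only sentence naming that outcome, together with Study Design, specifies recurrent TIA. The objective, data collection, powered comparison and descriptive analysis specify recurrent vascular events. Given the Background's definition of TIA, a stroke-only patient is an event under one and not under the other, so the stated primary outcome does not fully answer the primary objective.

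The size is up to about 3 to 9 of 86 evaluable patients at the quoted 4–10% stroke risk, or about 2 at the quoted 2.1%, against about 19 events at the planning rates. This rests on 5% dropout, on the quoted risks applying to this population, and on these patients having no TIA in the same window. Dilution of the PWI comparison is conditional on strokes concentrating in PWI-positive patients. The point should be settled before analysis, because the primary result depends on it and the remedy is cheap.

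**What to change.** 1. Name one 7-day primary outcome that matches the primary objective and includes stroke, and list its component events. Any recurrent ischemic event, meaning TIA or ischemic stroke, is one example.
2. Use that outcome in the Abstract, Study Design, Primary Objective, Sample Size and Power Calculation, and Statistical Analysis. Report TIA and stroke separately as components.
3. In Study Design, label 3-month recurrence and mRS as secondary, as the Abstract does.
4. In Sample Size and Power Calculation, state the endpoint and time window to which the 10% and 34.8% rates refer, and restate the power for the chosen outcome. The 34.8% equals the 3-month recurrent-TIA proportion over both pilot groups in the Background, (14 + 2)/(34 + 12) = 16/46, so its event and window both need confirming.

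Procedures already collects vascular events at both follow-up visits, so no new data collection appears necessary. The cost is revised wording and a fresh power statement. The small downside is that the stated power may change, in either direction.

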### Procedures

Ninety patients will be recruited in the next 1.5 years based on the calculation of the authors. Baseline assessments will be completed when the participants visit the neurology clinic of Shanghai Fourth People's Hospital or Tongji Hospital. The first PWI will be completed within 24 h after onset, and the subsequent PWI will be completed on the 7th day ± 2. Three visits to the hospital are required, which include the first visit for randomization (baseline) and the next two for repeat PWI on day 7 ± 2 and follow-up on 90 ± 7 days. The incidence of recurrent vascular events will be collected from all the patients on the second and third visits. Meanwhile, etiological subtypes (large artery occlusive disease, small vessel disease, cardioembolism, etc.) should also be considered for reasons of early recurrent stroke (Purroy et al., 2007). Baseline and follow-up assessments are summarized in Table 1.

**Table 1 T1:** Trial schedule.

**Assessment**	**Screening (within 24 h of symptoms onset)**	**Visit 1**	**Visit 2**	**Visit 3**
		**Baseline**	**Day 7 ± 2**	**Day 90 ± 7**
Demographic characteristics	×			
ABCD2 score (for TIA)	×			
Modified Rankin Scale	×		×	×
Focused medical history	×^a^			
Current medications	×^b^		×	×
MRI scan	×			
MRI PWI		×	×	×
Laboratory tests	×			
Electrocardiograph (ECG)	×			
Inclusion/Exclusion criteria	×			
Signed informed consent	×			
AEs/SAEs^c^		×	×	×
Incidence of recurrence			×	×

*AE, adverse event; SAE, serious adverse event; TIA, transient ischemic attack; ABCD2, a risk assessment tool designed to improve the prediction of short-term stroke risk after transient ischemic attacks*.

a *Relevant existing data from admission to hospital will be reviewed and recorded into the CRF. Included are concomitant diseases and medical history*.

b *The medications used during the trial should be recorded*.

c *SAEs will be recorded from the time of informed consent. AEs of interest and endpoints will be collected from the time of admission to the hospital*.

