### Statistical Analysis

The proportion of patients with recurrent vascular events on days 7 and 90 will be presented as frequency (percentage). Continuous variables will be presented as mean ± SD or median with interquartile range (IQR). Categorical parameters are presented as independent proportions. Baseline information of patients with or without hypoperfusion abnormalities is compared using the Mann-Whitney *U*-test or *t*-test for continuous variables and Fisher's exact test or χ^2^ for categorical variables. Logistic regression analysis will be performed to compare the proportion of recurrence between the two groups. *P* < 0.05 (two-sided) is considered statistically significant. Data analysis will be performed using IBM SPSS (version 20.0) for Windows (SPSS Inc., Chicago, IL, USA). The Data and Safety Monitoring Board will conduct an interim analysis on 45 patients (half of the required sample size). *P* < 0.05 is considered statistically significant in the interim and final analyses.

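### The 3-month mRS is compared between non-randomised PWI groups by an unadjusted rank-sum test; stratifying by pre-event mRS (0 v 1) is a free, minor improvement

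*Protocol article*

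**What the plan says.** The Abstract gives the status of the outcome, "Secondary outcomes will be the recurrence of TIA in 3 months and modified Rankin scale (mRS) score", and its test, a "rank sum test in the mRS score". The sentence that follows confines adjustment to the other outcome: "Multivariate logistic regression will be simultaneously performed to analyze the risk factors for the recurrence of TIA". Study Design names "the mRS score in 3 months" among the main outcomes and says how the groups arise: "According to baseline MRI-PWI examination, the patients are divided into the PWI positive and PWI negative groups".

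The Statistical Analysis section does not mention mRS. For the group comparison it says "Logistic regression analysis will be performed to compare the proportion of recurrence between the two groups". Baseline differences are only to be described: the relevant sentence begins "Baseline information of patients with or without hypoperfusion abnormalities is compared using the Mann-Whitney" and goes on to other two-group tests.

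Two further places matter. Table 1 (Procedures) has a row "Modified Rankin Scale" marked at screening, day 7 and day 90, with screening placed within 24 hours of onset. The Exclusion Criteria bar anyone with a pre-stroke mRS of 2 or more.

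**The concern.** In a cohort grouped by a scan result, patients with and without hypoperfusion may differ in function before the index event. A rank-sum test on the 3-month score alone cannot tell disability that was already there from disability that followed.

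The entry limit leaves only a 0 v 1 difference, but that difference can still count. If many patients return to their own baseline after a TIA (an assumption; the documents do not say), most 3-month scores are 0 or 1 and follow the entry score. That split is then much of what the rank test sees. An excess of 1s among PWI-positive patients would look like a worse outcome with hypoperfusion; an excess among PWI-negative patients would hide one. The plan adjusts for recurrence but not for mRS, in the same groups.

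**Working it through.** **The plan's own figure.** The only sample size stated is 90, for recurrence (34.8% v 10%, two-sided 5%, 80% power, 1:1, 5% dropout). The arcsine formula gives 41.05, so 42 per group; 42/0.95 = 44.2, so 45 per group and 90 in total. It reproduces and is not affected by this point. No figure is stated for mRS.

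**Inputs.**
- From the document: 90 patients, 5% dropout and 1:1 give 90 × 0.95 / 2 = 42.75, taken as 43 per group. Pre-event mRS is 0 or 1.
- Assumed: the share with baseline mRS 1 in each PWI group, and how the score moves by 3 months. There is no PWI effect in any setting.

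**Formula.** The rank-sum test targets θ = P(PWI+ score higher) + ½ P(tie), which is 0.5 under no difference. With average category shares p, its null standard deviation is √[(N+1)/(12·43·43) × (1 − Σp³)], and (N+1)/(12·43·43) = 87/22,188 = 0.003921. With z = (θ − 0.5)/SD, the rejection rate is about Φ(z − 1.96) + Φ(−z − 1.96).

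**Model 1: 80% unchanged, 12% one point worse, 8% two points worse.** With baseline mRS 1 in 40% v 20%, the 3-month shares at scores 0, 1, 2, 3 are:
- PWI+: 0.480, 0.392, 0.096, 0.032
- PWI−: 0.640, 0.256, 0.088, 0.016

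θ = 0.3684 + ½ × 0.4165 = 0.5766. The averaged shares 0.560, 0.324, 0.092, 0.024 give 1 − Σp³ = 0.7896 and SD = 0.0556. So z = 0.0766/0.0556 = 1.38, and the rejection rate is about 28%. Simulation (4,000 trials per setting) agrees:

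| Baseline mRS 1, PWI+ v PWI− | Formula | Simulated, unadjusted | Simulated, stratified |
|---|---|---|---|
| 30% v 30% | 5.0% | 4.7% | 4.5% |
| 35% v 25% | 10.6% | 10.3% | 4.9% |
| 40% v 20% | 28.1% | 28.2% | 4.7% |

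**Model 2: 8% have a disabling event; a share r of the event-free keep their score.** For the formula I let the remaining event-free patients swap between 0 and 1. With an imbalance of Δ in the share at 1, θ − 0.5 = ½ × 0.92² × (2r − 1) × Δ. For r = 0.9 and Δ = 0.20 this is ½ × 0.8464 × 0.8 × 0.20 = 0.0677; SD = 0.0540, z = 1.25, rejection 24%. Simulated values come from 4,000 or 6,000 trials per setting:

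| r | 35% v 25%: formula | simulated | 40% v 20%: formula | simulated |
|---|---|---|---|---|
| 90% | 9.6% | 9.5–9.7% | 24.0% | 24–24.3% |
| 75% | 6.7% | 7.1–7.3% | 11.9% | 11.4–12.3% |
| 60% | 5.3% | 5.2% | 6.1% | 5.9% |

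A 5-point imbalance (30% v 25%) at r = 90% gives 6.2% by formula and 6.6% simulated. The factor (2r − 1)Δ shows that both conditions are needed: with no imbalance, or with little carry-over of the baseline score, the excess vanishes.

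**Stratified test.** Within a baseline stratum the two groups share one 3-month distribution under the null, so the van Elteren test should hold its level. Simulated rates run from 4.5% to 5.3%; the Monte Carlo standard error at 4,000 trials is √(0.05 × 0.95/4,000) = 0.34%.

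**Direction.** Exchanging the two shares changes the sign of θ − 0.5 and leaves the rejection rate the same.

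**The case against.** The strongest objection is that the bias needs an imbalance the documents never show. No mRS distribution is given, and nothing links PWI status to prior function. The retention of baseline mRS is undocumented too, and at 60% retention the inflation is almost gone. This stands, and it is why the result is a range that starts at the nominal level.

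The entry criterion removes any difference of more than one point per patient. That stands as a limit on the problem; it does not remove it, as the tables show.

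Table 1's score is taken after onset and is not said to be the pre-event score. It may reflect the index event, and stratifying on it could remove part of the association under study. This stands and changes the remedy.

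The study's stated aim is mainly prediction, so a crude comparison is a legitimate description. That supports keeping it as descriptive. It does not support making it the only mRS comparison when Study Design lists mRS among the main outcomes and recurrence is adjusted.

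Finally, a condensed article may leave covariates to an analysis plan not shown. But the article does name a test for mRS and limits the multivariable model to recurrence. That is a stated choice, not an omitted detail.

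**Conclusion.** The point holds as a minor one. The only mRS comparison stated is unadjusted, in groups formed by a scan result. Any difference between the groups in the share entering at mRS 1 would bias it. Under assumed imbalances of 10 to 20 points and assumed retention of 60% to 90%, the null rejection rate runs from about 5% to 28%, against about 5% when stratified. The imbalance, the retention and the 43-per-group split are all assumptions.

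A reader might infer more in three ways, none of which the documents support:
- That the planned test has a false-positive rate of a quarter or so. That figure needs a 20-point imbalance and 80% to 90% retention together.
- That prior disability will make the PWI-positive group look worse. The direction of any imbalance is unknown.
- That marked pre-existing disability could pass for a hypoperfusion effect. The exclusion of pre-stroke mRS of 2 or more rules that out.

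The primary outcome and the sample size are not touched.

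**What to change.** Replace the unadjusted rank-sum test with one of these:
- a van Elteren test of 3-month mRS between PWI groups, stratified by pre-event mRS (0 v 1); or
- proportional-odds regression of 3-month mRS on PWI group, with pre-event mRS as covariate.

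State that the covariate is the pre-event score assessed for eligibility, not a post-onset screening score. Keep the crude comparison as descriptive.

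The cost is a line or two of analysis text and no extra patients or visits. Because eligibility only requires the score to be below 2, confirm that the case report form records whether it was 0 or 1. Adjusting for pre-event mRS alone leaves confounding by age, ABCD2 and other factors; the regression form could include these as well, as far as the sample size allows.

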**Trial Registration:**
www.chictr.org.cn, registration number: ChiCTR2000031863, registered on 12 April 2020.

## Background

Transient ischemic attack (TIA) has been defined as a short-lasting episode of neurological dysfunction without evidence of acute infarction (Easton et al., 2009). Approximately 24 million people experience TIA every year in China (Wang et al., 2015). Patients with recent TIAs are at a high risk for recurrent strokes or other vascular events (Lavallee et al., 2007; Amarenco et al., 2016). For example, patients with TIA have a 4–10% possibility of developing a stroke within 7 days and a 10–20% (average 11%) possibility within 90 days, much higher than the risk of developing recurrent strokes (2–7%, average 4%) within 90 days after an acute ischemic stroke (Kelly et al., 2016). Urgent diagnosis and treatment can significantly reduce the risk of recurrent ischemic events after TIA (Amarenco et al., 2016; Kim et al., 2016). A cohort study in the UK showed that optimal secondary prevention decreased the incidence of recurrent ischemic events after TIA from 10.3 to 2.1% (Rothwell et al., 2007).

A recent study raised the hypothesis that patients with TIA have different degrees of recurrence, depending on clinical symptoms, pathological mechanisms, and treatments (Kelly et al., 2016). How to identify TIA patients at high risk of recurrence and provide timely treatment is a problem that needs to be solved urgently in the clinic. The age, blood pressure, clinical symptoms, duration, and diabetes score (ABCD2, 0–7 points) is a stratified approach based on clinical manifestations. It aims to facilitate the evaluation of patients with stroke/TIA by non-neurology medical staff in the emergency room. For neurology professionals, its specificity is low (Amarenco et al., 2009; Giles and Rothwell, 2010; Wardlaw et al., 2015).

The morphological definition of TIA, that is, diffusion-weighted imaging (DWI)-negative TIA, did not clearly distinguish the tissue perfusion status of all patients with TIA. Low perfusion may be one of the mechanisms of TIA recurrence. Perfusion weighted imaging (PWI) is positive in 20–40% of patients with clinical TIA, while DWI is negative (Mlynash et al., 2009; Kleinman et al., 2012; Asdaghi et al., 2013; Grams et al., 2016; Lee et al., 2017). Previous studies have suggested that hypoperfusion might be associated with recurrent TIAs, stroke, and continued deterioration of neurological symptoms (Olivot et al., 2008; Asdaghi et al., 2011, 2013; Lee et al., 2017). The previous study conducted by the authors has assessed 66 patients with TIA with anterior circulation symptoms and found that hypoperfusion is present in 50% of the patients (33/66), with 31.8% (21/66) showing PWI-positive and DWI-negative findings (Wang et al., 2019b). In order to further explore whether the recurrence of TIA in patients with no lesions shown on DWI is related to hypoperfusion, 46 patients with normal DWI were followed up for 3 months in the study. The incidence of recurrent TIA was 41.2% (14/34) in the hypoperfusion group and 16.7% (2/12) in the normal perfusion group. There was a significant statistical difference between the two groups.

There are many modalities for assessing hypoperfusion. Although mean transit time (MTT) and time to peak (TTP) can be used to observe abnormal changes in perfusion in patients with TIA (Kleinman et al., 2012), time-to-maximum of residue function (*T*_*max*_) ≥ 4 s is currently the best one for evaluating perfusion abnormalities in the early stage (Olivot et al., 2009; Wang et al., 2019a,b). The previous results showed that the prevalence of *T*_*max*_ ≥ 4 s > 10 ml was 50% (33/66). Limb fatigue combined with *T*_*max*_ ≥ 4 s > 10 ml was an independent risk factor for recurrence (adjusted OR = 3.74, 95% CI = 1.02–13.64, *P* = 0.046). Therefore, it is feasible and clinically significant to use *T*_*max*_ ≥ 4 s to evaluate the perfusion status of patients with TIA.

The Prospective Cohort Study of Hypoperfusion in Predicting Recurrent Transient Ischemic Attacks (REATTACK) trial is, therefore, designed to explore the correlation between hypoperfusion and TIA recurrence as well as prognosis. By completing this prospective cohort study of patients with TIA with low perfusion (*T*_*max*_ ≥ 4 s > 10 ml), it is likely to further the insight into the pathological mechanism of TIA recurrence.

